### Power analysis

Power analyses for our proposed primary analysis was generated using the multilevel logistic regression module for proportions in a 2-level hierarchical design in NCSS PASS 21 [147]. We set the base rate of sustained viral suppression to 50% based on MPI [name]’s Suubi-Adherence study. We assumed *N* = 576 participants recruited from 48 clinics and set α = 0.05, power = 0.80, and the intracluster correlation (ICC) due to clustering of participants within clinics at 0.024 based on data from MPI [name]’s Suubi-Adherence study. We conservatively assumed 20% attrition (*N* = 480). The minimum detectable odds ratio is 1.77, which corresponds to a minimum raw proportion difference of 14% and a standardized effect size of 0.28, which is between a small to medium effect size. For Specific Aim 2, the only difference in power calculations was we set the base rate of sustained viral suppression to 75% and the ICC to 0.038 based on 12-month achieved VL suppression data from MPI [name]’s Suubi-Adherence study. Under these conditions, the minimum detectable indirect effect odds ratio is 1.80, which is between a small and medium effect size [148].

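### The Aim 2 minimum detectable odds ratio of 1.80 does not follow from the inputs given: the Aim 1 calculation with those inputs gives a total-effect odds ratio of about 2.14 to 2.19, and no indirect-effect figure can be derived

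*Protocol article*

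**What the plan says.** All the inputs stand in the Power analysis section of the protocol article.

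- **Common settings:** the authors "set α = 0.05, power = 0.80", with 576 "participants recruited from 48 clinics". They add "We conservatively assumed 20% attrition" and give the resulting sample as 480.
- **Aim 1:** "We set the base rate of sustained viral suppression to 50"%, with an ICC "due to clustering of participants within clinics at 0.024". Result: "The minimum detectable odds ratio is 1.77, which corresponds to a minimum raw proportion difference of 14"%.
- **Aim 2:** "the only difference in power calculations was we set the base rate of sustained viral suppression to 75% and the ICC to 0.038". Result: "the minimum detectable indirect effect odds ratio is 1.80".

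The Aim 2 sentence attributes its inputs to 12-month achieved suppression in the earlier study, although it labels the rate as sustained suppression. The section on secondary and economic outcomes also sets the mediation outcome as suppression at 12 months. The data analysis plan for secondary outcomes defines the mediation test as the product of the component-to-mediator path (a) and the mediator-to-outcome path (b), at alpha 0.05.

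**The concern.** Both Aim 2 changes make a given odds ratio harder to detect. Moving the base rate from 50% to 75% reduces the information a binary outcome carries about an odds ratio, and a larger ICC reduces the effective sample. Yet the detectable odds ratio rises only from 1.77 to 1.80.

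The label is a second difficulty. Mediation power depends on the sizes of the a- and b-paths and on the mediator's variance. If base rate and ICC are the only changes from Aim 1, none of these entered, and the result is a total-effect figure.

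Mediation is listed among the primary aims in the Background, and the analysis plan uses the separate paths to diagnose weak and strong components. Readers of those results will rely on the power statement.

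**Working it through.** **Inputs.** 480 analysed participants in 48 clinics, so 10 per clinic. Each component is compared as 24 clinics against 24, so 240 participants per level (from the 2^4 factorial with clinic randomization). Alpha 0.05, power 0.80. The article does not state sidedness. Two-sided is assumed because it reproduces Aim 1, whereas one-sided gives about 1.65 to 1.67 there.

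**Formulas.** Design effect DE = 1 + (10 − 1) × ICC. Effective n per level = 240 / DE. With unpooled variance, SE = √{[p0(1 − p0) + p1(1 − p1)] / n}. The detectable p1 satisfies (p1 − p0) / SE = 1.960 + 0.842 = 2.802. Power at a given p1 is Φ[(p1 − p0)/SE − 1.960].

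**Step 1: reproduce Aim 1.** DE = 1 + 9 × 0.024 = 1.216, and n = 240 / 1.216 = 197.4. At p0 = 0.50 and p1 = 0.638, SE = 0.0494 and 0.138 / 0.0494 ≈ 2.80. The odds ratio is 1.765 unpooled, 1.772 pooled and 1.779 on the log-odds scale. The stated 1.77, with a difference of 14 points, is recovered.

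**Step 2: change only the two Aim 2 inputs.** DE = 1 + 9 × 0.038 = 1.342, and n = 240 / 1.342 = 178.8. At p0 = 0.75 and p1 = 0.8655, SE = 0.0412 and 0.1155 / 0.0412 ≈ 2.80. The odds ratio is (0.8655 / 0.1345) / 3 = 2.145.

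| Variance form | Aim 1 OR | Aim 2 OR | Aim 2 upper rate | Total-effect power at OR 1.80 |
|---|---|---|---|---|
| Unpooled | 1.765 | 2.145 | 86.5% | 0.602 |
| Pooled | 1.772 | 2.159 | 86.6% | 0.597 |
| Log-odds | 1.779 | 2.194 | 86.8% | 0.590 |

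For the last column, OR 1.80 from 75% means odds of 5.4, so p1 = 5.4 / 6.4 = 84.4%. Unpooled, SE = 0.0423, z = 0.09375 / 0.0423 = 2.22, and power = Φ(2.22 − 1.96) ≈ 0.60.

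**Step 3: the ICC change alone.** With the base rate left at 50% and the ICC raised to 0.038, the three forms give 1.82 to 1.83. That is already above 1.80, before the costlier move to 75%.

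**Step 4: look for a route to 1.80.** Two-sided unless stated.

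- No attrition (N = 576, DE 1.418): 2.03 to 2.07.
- A true 20% loss from 576 (N = 461): 2.17 to 2.23.
- 75% taken as the overall mean rate, N = 480: 1.90 to 2.02.
- Log-odds with variance fixed at the base rate: 1.98 (this form gives 1.76 for Aim 1).
- A decrease from 75%, N = 480: 1.89 to 1.98.
- A one-sided decrease: 1.77 to 1.84, but one-sided testing does not fit Aim 1.
- N = 576 with no clustering: 1.80 (pooled). N = 480 with no clustering and variance at the base rate: 1.805. The same shortcuts give 1.60 and 1.67 for Aim 1.

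Values near 1.80 therefore appear only when a stated input is dropped or a one-sided test is used. Each of those choices fails to return 1.77 for Aim 1.

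**The case against.** The strongest reply is that 1.80 is labelled an indirect effect, so a two-group calculation is the wrong yardstick. The software module is named for the primary analysis, the Aim 2 result carries its own citation, and the article condenses a longer protocol. A separate mediation calculation with unreported path sizes may exist. The same sentence is loose elsewhere, since it calls a 12-month rate sustained.

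Part of this stands. A reader might infer from the 60% that Aim 2 is underpowered and that null mediation results would be over-interpreted. The document does not support that inference, because the 60% belongs to a total-effect comparison and the planned test is a product of paths. Power for that test depends heavily on how the effect divides between the paths. A simulation with assumed path sizes illustrates this (48 clinics of 10, ICC 0.038 on mediator and outcome, a standardized continuous mediator, no direct effect, joint-significance test, 400 runs per setting). For an indirect odds ratio of 1.80 it gave power of about 1.00 with equal paths (0.767 each), 0.78 with a = 0.30 and b = 1.96, and 0.70 with a = 0.25 and b = 2.35. The true power could lie on either side of 80%.

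The reply does not rescue the text. A separate mediation calculation would contradict the statement that base rate and ICC were the only differences. One of the two statements must change.

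**Conclusion.** Wrong as written, moderate severity. On the basis the article describes, the minimum detectable odds ratio for Aim 2 is a total-effect figure of about 2.14 to 2.19, and total-effect power at 1.80 is about 60%. This rests on a two-sided test, 10 analysed participants in each of 48 clinics, equal allocation on each component, and an increase from 75%. The spread reflects the three variance forms in the table, all of which reproduce Aim 1. The cruder form with variance fixed at the base rate gives 1.98, still well above 1.80.

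Power for the planned indirect-effect test is unknown from the document. Neither 60% nor 2.14 should be read as describing it.

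The error does not reach the primary analysis: the Aim 1 figure reproduces and the sample size is unchanged. Although mediation appears among the primary aims, it is analysed under secondary outcomes, and correcting the sentence alters no test or alpha level.

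**What to change.** Remove the claim that an indirect-effect odds ratio of 1.80 is detectable under these conditions. Then do one of the following.

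1. Restate the figure as a total-effect minimum detectable odds ratio of about 2.14 to 2.19 (75% against about 86.5 to 87%), and say plainly that it is not power for the mediation test.
2. If an indirect-effect figure is kept, derive it by simulation with stated a- and b-path sizes, mediator assumptions and clinic clustering, and delete the statement that only the base rate and ICC differ from Aim 1.

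In either case, name the outcome as 12-month suppression instead of sustained suppression. The first option costs rewording and a less favourable stated figure; the second adds a short simulation. Neither changes the design or the sample size.

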### Determining the Optimized Intervention

The operational definition of an optimized intervention is one that produces the most cost-effective outcome while meeting the optimization objective, the most cost-effective outcome under our pre-defined real-world constraints (i.e., efficiency, affordability, and scalability). Within the MOST framework, there are two key perspectives to how determine optimization. First, in a *conclusion-priority perspective*, optimization is based solely on the statistical significance at *p* < 0.05 of each component (rejection of the null hypothesis) [141]. However, if a component or an interaction effect failed to reject the null hypothesis, it is not known whether that component or that interaction genuinely had an effect on viral suppression or if a Type II error (incorrect rejection) was made. This perspective (i.e., *p* must be less than 0.05 alone) may erroneously suggest that one or more components should not be included in the optimized intervention. In a *decision-priority perspective* [141], the components and interactions that evidence a statistically significant effect may or may not be included in the optimized intervention as their inclusion depends on the optimization objective – most cost-effective outcome under our pre-defined real-world constraints (i.e., efficiency, affordability, and scalability). For example, our primary analysis will identify the combination of components that produce the greatest odds for sustained viral suppression at *p* < 0.05. However, regarding optimization, if the difference in the odds between having 3 and 4 components is 5%, we could evaluate whether that difference is worth the burden, time, or cost to implement the fourth component. Or, three components could synergistically interact and produce an effect equivalent to having all four components delivered. In a decision-priority perspective, optimization does not have to be based on statistical significance alone but on identifying the costs, effect sizes, and feedback from staff and investigators on the best number of components for sustained viral suppression among ALHIV.

## Discussion

The Suubi + Adherence4Youth study is following the shift in the paradigm of research to use new thinking to build/un-pack highly efficacious interventions that lead to new scientific knowledge in terms of understanding what drives an intervention’s success and how to iterate on them in ways that are more efficient, affordable and scalable [73]. The concept and methods proposed to critically reflect and test our prior Suubi intervention advances intervention science during a critical period of time for a vulnerable group – as ALHIV transition through young adulthood. Most HIV prevention, care and support efforts in SSA communities are “transported” from outside the region, mainly from the global north [1–7], and offer limited information in understanding why or how they are affected by the low-resource context. Yet, this knowledge is imperative, and it is important to note that the Suubi intervention strategies are developed and tested within the global south’s existing institutions and infrastructure. Moreover, Suubi + Adherence4Youth has additional important advantages: it is theoretically driven; comprehensive, and carries a range of contextual and modifiable components that make it ideal for scale up. We are addressing structural economic factors that constitutes a major gap in HIV intervention science, especially in the context of resource-constrained settings. Most existing interventions were developed and implemented in high-income developed societies with sufficient human and financial resources available to support well-functioning social welfare systems [104]. As a result, in poorer countries where resources are limited, dissemination of such interventions are restricted. Among 14 intervention studies reviewed, findings showed that participants’ adherence improved slightly in nine studies, while in three intervention effects were sustained over time [149, 150]. However, the majority of interventions utilize cognitive behavior models [149, 150] and thus there are difficulties in sustaining the effects of psychosocial interventions over time.

Thus, while short-term psychosocial interventions have become an accepted strategy to manage the staggering numbers of HIV patients—registering small to moderate effect sizes at best [149, 150]– a failure to explicitly address economic hardships will limit the degree to which we can meaningfully improve HIV care outcomes. The Suubi + Adherence4Youth study is primarily interested in viral suppression via economic and psychosocial support systems. In the context of resource-poor countries, interventions that improve families’ economic capabilities are likely to be particularly consequential. This study will employ a highly efficient MOST framework that will allow us to understand the role each component in the Suubi intervention plays in producing the outcome across 48 health clinics in Uganda for a large sample of ALHIV. This is innovative because the approach may yield an optimized intervention that can be progressively refined for other resource constrained countries in SSA—one of the world’s poorest regions with the highest HIV prevalence. Taken as a whole, this innovative approach can pave the way for other researchers to build directly from our conceptual model and evidence base in a way that is transparent and forward thinking. The proposed study offers us an opportunity to cost each of the four components and every combination of Suubi components to achieve a unit of effect across the primary outcome. This may offer insights in regards to potential for scale-up in real-world constraints.

## Data Availability

Not applicable.

## Abbreviations

AIDS: Acquired Immunodeficiency Syndrome
ALHIV: Adolescents living with HIV
ANOVA: Analysis of Variance
ART: Antiretroviral Therapy
CEA: Cost-Effectiveness Analysis
CRT: Cluster Randomized Trial
DSMB: Data and Safety Monitoring Board
FLT: Financial Literacy Training
GEE: Generalized Estimating Equations
GLM: General Linear Model
HIV: Human Immunodeficiency Virus
ICC: Intracluster correlation
ICER: Incremental Cost-Effectiveness Ratio
ICHAD: International Center for Child Health and Development
IGA: Income-Generating Activities
IRB: Institutional Review Board
MAR: Missing-At-Random
MI: Multiple Imputation
MIS IDA QC: Management Information System for Individual Development Accounts Quality Control
ML: Maximum Likelihood
MOST: Multi-phase Optimization Strategy
MPI: Multiple Principal Investigator
NIH: National Institutes of Health
RA: Research Assistant
RCT: Randomized Controlled Trial
RHSP: Rakai Health Sciences Program
RTY-Uganda: Reach the Youth Uganda
SSA: Sub-Saharan Africa
UNCST: Uganda National Council of Science and Technology
USD: United States Dollar
UVRI: Uganda Virus Research Institute
WUSTL: Washington University in St. Louis
YSA: Youth Savings Accounts
